### Sampling VDTs

On a monthly basis, after excluding dates for holidays and related events, a sample is drawn from the sampling frame based on the number of planned recruitment events per month. This involves a two-stage sampling process: first a simple random sample of venues, then for each sampled venue, a random sample of associated time blocks. Sampling is done without replacement for each month, but previously selected VDTs are eligible for sampling in subsequent months. For each selected VDT, we also sample two alternate VDTs in the event that recruitment within the main VDT is infeasible due to safety concerns or low attendance. One week prior to the recruitment event, study staff members observe the selected venue to determine its suitability with respect to safety and other logistical concerns. Study staff also secures a location to conduct confidential study activities, or used a large mobile van. We will conduct up to 4 VBS events per month over 30 months for a total sample size of 400 participants enrolled.

### Eligibility criteria

The VBS eligibility criteria are the same as in the PDI/RDS study described above, with the following exceptions: VBS participants must reside in the core HRA (not the larger HRA), and those with previously diagnosed HIV are ineligible. Thus, the VBS eligibility criteria are: aged 18-60 years; sexually active (vaginal and/or anal sex) with at least one opposite sex partner within the previous year; reside in the core HRA’s seven zip codes; African American/Black or Latino/Hispanic race/ethnicity; comprehend English or Spanish; unknown or negative HIV status; not actively psychotic based on valid screening instrument.

### Primary outcome measure

The primary outcome is the yield and efficiency of VBS to identify undiagnosed HIV infection among HHR, which will be compared to rates in the RDS sample. HIV status is assessed with the OraQuick Advance Rapid HIV-1/2 Antibody Test using oral fluid and OraSure Western Blot for confirmatory testing using oral mucosal fluids.

### Description of study activities

#### Enrollment targets

The goal is to enroll 6 to 9 participants at each event. The field team is comprised of a supervisor, a HIV test counselor/interventionist (who deliver HIV test results), and 2-3 Research Associates. At least one staff member at every event is a trained phlebotomist. Team members include both males and females from diverse socio-economic and racial backgrounds who are knowledgeable about, comfortable with, and experienced with the local area, target population, and field recruitment methods. As in the BCAP PDI, the overarching counseling approach is Motivational Interviewing [46].

At the enrollment event, participants who cross a pre-specified recruitment line in the selected venue are approached by a staff member and recruited for the screening interview. All those who cross this line are counted to enumerate the venue size. Individuals who cross the line are asked if they would be willing to participate in a brief (15 min) health screening interview for a community health study, depending on staff availability. We estimate 50-75 % of participants who cross the line will be approached.

A brief screening interview determines study eligibility. Those who consent to participate but who are unable to complete the study activities at that time may complete activities at the study field site location within two weeks of recruitment.

Participants then engage in HIV pre-test counseling and receive a rapid OraQuick HIV test. During the 20-min processing period, the participant completes a structured baseline interview using ACASI, which measures socio-demographic and background factors, health, substance use, sexual behavior, and HIV testing history using a battery of measures collected across all NIDA STTR projects [81–83].

Participants with a non-reactive (negative) test result receive risk reduction counseling. Those with reactive test results are informed about the preliminarily positive result, and the need for confirmatory testing. A confirmatory test is conducted, and the interventionist initiates a brief discussion about this new diagnosis, individually tailored in light of the wide variety of participant reactions to HIV diagnoses [84]. Then the interventionist discusses the need for HIV primary care and makes an appointment for HIV primary care at a setting the participant finds convenient and acceptable. Third, the interventionist informs the participant that all those who test preliminarily positive are asked to give blood specimens, in order to document the initial health status of those with new diagnoses. In the final component of the post-test counseling session, participants are provided with the interventionist’s contact information, for support, referrals, or any other concerns and are scheduled for a return appointment for the confirmatory test result at the project field site two-weeks later. Participants receive compensation at an equivalent rate to the PDI/RDS study.

### Power analysis

For the Seek and Test study aim, 3000 HHR recruited by RDS are compared with 400 HHR recruited by VBS on the outcome of newly diagnosed HIV infection. Assuming 10 % of the RDS sample will have newly identified HIV infection, the study is powered to detect a difference in seek approaches of OR = 1.79 with 80 % power (α = .05). If the intraclass correlation (ICC) for previously undiagnosed HIV infection is as high as .20 (due to clustering of individuals within 80 recruitment chains), the effective sample size is as low as *n* = 361 in the RDS group, and OR = 2.25 is detected with 80 % power (α = .05).

### Analysis plan

We will examine differences in demographic characteristics between VBS and RDS participants and adjust for these when comparing VBS and RDS. The guiding hypothesis for the Seek and Test aim is the following: compared with VBS, and controlling for potential differences on key socio-demographic characteristics across the samples, participants recruited by RDS will be more likely to be newly diagnosed with HIV. This hypothesis is assessed using logistic regression analysis. Newly diagnosed HIV infection (Yes/No) is regressed on a dummy variable created to contrast participants recruited at venues with participants recruited by RDS. If the coefficient for this variable is positive and significant, we will conclude that RDS is a more effective approach for seeking HHR likely to have undiagnosed HIV infection. Covariates will include prior HIV testing.

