#### Venue-based sampling (VBS)

VBS is a method to systematically recruit individuals in a target population who may be hard-to-reach, but who may be located and engaged in identifiable venues such as parks and hair salons. VBS has proven successful in identifying populations at high risk of HIV infection, mainly MSM [74–76], but also heterosexuals in the U.S. and globally [77, 78]. VBS starts by identifying days and times at which the target population gathers at specific venues, constructing a sampling frame of venue-day-time units (VDTs), randomly selecting and visiting VDTs (the primary sampling units), and systematically intercepting and collecting information from consenting members of the target population [74].

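### The RDS-versus-VBS logistic regression states no allowance for clustering by recruitment chain or venue event, so at the protocol's own upper ICC of .20 its two-sided type I error would be about 15%

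*Protocol article*

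**What the plan says.** The Analysis plan of Part 2 names the model, the contrast, the covariates (socio-demographic differences and prior HIV testing) and the decision rule. The model is logistic regression: "Newly diagnosed HIV infection (Yes/No) is regressed on a dummy variable created to contrast participants recruited at venues with participants recruited by RDS". A positive coefficient that reaches significance leads to the conclusion that RDS is more effective. Neither recruitment chains nor venue events appear in the model or its variance.

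The Power analysis of Part 2 does consider chains. It sets out the comparison, "3000 HHR recruited by RDS are compared with 400 HHR recruited by VBS on the outcome of newly diagnosed HIV infection", and reports that "the study is powered to detect a difference in seek approaches of OR = 1.79 with 80 % power (α = .05"). It then adds a scenario: "If the intraclass correlation (ICC) for previously undiagnosed HIV infection is as high as .20". In that case the RDS sample shrinks to an effective 361, and the stated result is that "OR = 2.25 is detected with 80 % power (α = .05"). The protocol explains that this correlation arises "due to clustering of individuals within 80 recruitment chains".

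The section Venue-based sampling (VBS) describes the method as "randomly selecting and visiting VDTs (the primary sampling units"), so the VBS sample is also a cluster sample. No design effect is applied to it in the Power analysis.

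In Part 1, Data analysis does name a clustered method (frailty models by recruitment chain), but only for time to first clinic appointment and time to ART.

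**The concern.** Two parts of the plan treat the same outcome in the same comparison differently. The Power analysis accepts that people in one chain may resemble each other enough to remove most of the RDS information. The Analysis plan describes a model whose usual standard error counts every participant as independent.

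With positive within-cluster correlation, that standard error is too small and the interval too narrow. False findings become more frequent in both directions, including the direction the investigators expect. This is the only hypothesis test that the Analysis plan of Part 2 specifies, and the Discussion says the comparison will guide the choice of the more efficient and cost-effective way to find undiagnosed infection. The OR of 2.25 in the Power analysis also applies only to an analysis that accounts for chain clustering, which the Analysis plan does not describe.

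**Working it through.** **Inputs from the protocol.** RDS n = 3000, VBS n = 400, 10% newly diagnosed in RDS, 80 chains, ICC up to .20, α = .05 (Power analysis, Part 2). VBS events: a target of 6 to 9 participants each (Enrollment targets). Up to 4 events a month for 30 months gives at most 120 events, or 400/120 = 3.3 per event (Sampling VDTs).

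**Step 1: reproduce the plan's figures.**
- Mean chain size: 3000/80 = 37.5.
- Design effect: 1 + (37.5 − 1) × .20 = 8.3.
- Effective RDS n: 3000/8.3 = 361, as stated.
- Detectable OR at 80% power (two-proportion test, pooled variance, two-sided .05, RDS 10%, VBS lower): 1.788 at n = 3000 and 2.245 at n = 361, matching 1.79 and 2.25. One-sided versions give 1.65 and 2.01, so the plan's α is evidently two-sided.

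**Step 2: size of the unadjusted test.** Under the null, with the same prevalence in both samples, the ratio of true to assumed variance is

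R = (DE_RDS/3000 + DE_VBS/400) / (1/3000 + 1/400).

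The prevalence cancels. The two-sided error is 2 × [1 − Φ(1.96/√R)], and the error in the positive direction is half of that.

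At ICC .20, equal chains and no venue effect:
- R = (.002767 + .002500)/(.000333 + .002500) = 1.859, and √R = 1.363.
- 1.96/1.363 = 1.438, so the two-sided error is 15.1% and the positive-direction error 7.5%.

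**Step 3: other chain ICCs (equal chains, no venue effect).**

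| ICC | DE, RDS | R | Two-sided | Positive direction |
|---|---|---|---|---|
| .02 | 1.73 | 1.086 | 6.0% | 3.0% |
| .05 | 2.825 | 1.215 | 7.5% | 3.8% |
| .10 | 4.65 | 1.429 | 10.1% | 5.1% |
| .20 | 8.3 | 1.859 | 15.1% | 7.5% |

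A beta-binomial simulation with 20,000 replicates agrees. At ICC .20 it gives 15.0% two-sided and 6.5% in the positive direction. With no clustering the same simulation gives 5.0% and 2.1%.

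**Step 4: two assumptions that the documents do not supply.**
- *Venue ICC of .20, chain ICC of .20.* At 3.3 per event, DE_VBS = 1 + 2.33 × .20 = 1.47, R = 2.271 and the two-sided error is 19.3%. At 9 per event, DE_VBS = 1 + 8 × .20 = 2.6, R = 3.271 and the error is 27.9%. The positive-direction error is 9.7% to 13.9%.
- *Unequal chains, CV of chain size 1, no venue effect.* DE_RDS = 1 + [(1 + 1²) × 37.5 − 1] × .20 = 15.8, R = 2.741 and the two-sided error is 23.6%. At ICC .05 the same CV gives 10.2%.

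**The case against.** The strongest reply is that this is a condensed article. The variance estimator is often left to the full analysis plan, which is not shown. The authors clearly know about the clustering: they quantify it for this comparison, define each seed and its recruits as a cluster, and name frailty models in Part 1. Nothing says that observations will be treated as independent. This stands in part: a reader might infer that the investigators have decided to ignore clustering, and the text does not show that. However, the Analysis plan goes as far as attaching a conclusion to one coefficient, and the article names a clustered method where it plans one. Followed literally, the stated analysis is anti-conservative, which is more than a missing detail.

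Three further points stand and limit the size of the claim.
- A reader might take 15% as a minimum. It is the value at the plan's own upper ICC; smaller ICCs give 6% to 10% from chains alone.
- A reader might set 15% against 5% for the decision rule itself. That rule counts only positive results, so its own comparison is 7.5% with 2.5%.
- Figures above 15% need a venue ICC or a chain-size CV, and the protocol gives neither. Unequal chains are plausible, since some chains stopped early (Changes to procedures during implementation) and new diagnoses bring extra coupons (Network-based case finding), but the degree is unknown.

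It is also fair that the Power analysis presents clustering as a conditional scenario beside the unclustered 1.79, and that the Aims section makes Treat and Retain the main aim.

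**Conclusion.** The concern holds in qualified form. The Analysis plan of Part 2 fixes a model and a decision rule without stating how chain or venue-event clustering enters, although the Power analysis and the VBS section both recognise clustered sampling. Chain clustering alone roughly triples the false-positive rate at the protocol's upper ICC. At an ICC of .05 the excess is modest, and at every positive ICC examined the error is in the anti-conservative direction. These figures assume the null hypothesis, equal chains, independence within venue events and no effect of covariate adjustment on the variance ratio. The higher values (about 19% to 28% with an assumed venue ICC of .20, about 24% with an assumed chain-size CV of 1) show sensitivity only. The documents do not support an unconditional rate of 15% or more.

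**What to change.** In the Analysis plan of Part 2, specify a GEE or mixed logistic model, or logistic regression with cluster-robust standard errors. Use the seed's chain as the cluster for RDS participants and the venue event (VDT) for VBS participants. State that the decision rule applies to the coefficient and standard error from that model. Because Sampling VDTs lets a unit be drawn again in later months, say whether repeat visits count as one cluster.

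The change is wording. Coded coupons already link recruit to recruiter, and events are scheduled units, so no new data are needed. The price is wider intervals and less apparent power. At an ICC of .20 the detectable OR becomes about 2.25 instead of 1.79, and larger if venue events are correlated, because the effective n of 361 discounts only the RDS side.

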## Discussion

The present study seeks to examine two approaches to uncovering undiagnosed HIV infection in an under-studied population: heterosexuals at high risk for HIV. Further, it tests components to link those with HIV-infection to HIV primary care with high retention, both newly diagnosed and those with previous HIV diagnoses. Study results will provide guidance on the most efficient and cost-effective means of uncovering this largely hidden and vulnerable population (by comparing RDS vs. VBS), and to link HIV-infected individuals to HIV care (by comparing the PDI arm vs. control). The ultimate aim of the present study is to provide an efficient, cost-effective, reproducible, and scalable sampling method and intervention approach to address the critical public health problem of undiagnosed HIV infection and delays in engagement in HIV care among HHR. This protocol provides background for other investigators interested in researching this population, which is challenging to define, reach, and engage.
